#### Participants and eligibility criteria

Participants with mild to moderate disease severity will be recruited (Hoehn and Yahr stages I–III). The eligibility criteria (inclusion and exclusion) are in agreement with the Mobilise-D study and are detailed in table 1. Potential participants will not be recruited if they have received and/or are due to receive a medication review within 4 weeks of the study assessment. Individuals with more advanced Parkinson’s (Hoehn and Yahr stages IV and V) often possess a decreased ability to efficiently perform activities of daily living and experience cognitive impairment. These factors may induce difficulties to monitor mobility and alter the participant’s ability to interact with the DHTS, respectively. Consequently, only individuals at Hoehn and Yahr stagess I–III will be recruited in this study.

**Table 1 T1:** Inclusion and exclusion criteria

Inclusion criteria	Exclusion criteria
Adults aged 18 or over	Occurrence of any of the following within 3 months prior to informed consent: myocardial infarction, hospitalisation for unstable angina, stroke, coronary artery bypass graft, percutaneous coronary intervention, implantation of a cardiac resynchronisation therapy device, active treatment for cancer or other malignant disease, uncontrolled congestive heart disease (New York Heart Association (NYHA) class >3), acute psychosis, major psychiatric disorders or continued substance abuse
Ability to consent and comply with study specific procedures	History consistent with Dementia with Lewy bodies, atypical parkinsonian syndromes (including multiple system atrophy or progressive supranuclear palsy, diagnosed according to accepted criteria)
Able to read and write in English	Repeated strokes or stepwise progression of symptoms, leading to a diagnosis of ‘vascular parkinsonism’
Patients with the clinical diagnosis of Parkinson’s according to the Movement Disorder Society criteria^47^	Drug-induced Parkinsonism
Hoehn and Yahr stages I–III^48^	
On stable Parkinson’s medication doses (taking the same medication for 4 weeks or more)	
Able to walk 4 metres independently with or without walking aids	
Willingness to wear and interact with a smartwatch and IMU, and carry a smartphone	

IMU, inertial measurement unit.

### Study assessments

At the beginning of the study, all participants will complete a clinic-based assessment including a range of general, clinical, Parkinson’s-specific, and physical assessments (box 1). These assessments will be performed during a Mobilise-D visit or within 14 days of the screening appointment for those recruited independently. Following assessment completion, participants will be equipped with a novel DHTS to wear and interact with over seven consecutive days and will complete a motor complications diary (ON-OFF-Dyskinesia) each day. Participants will be free to withdraw from the study at any time, without providing reasoning and they will be given a contact point to obtain further study information.

Box 1Outcome measuresGeneral measuresDescriptive measures (year of birth, sex, living arrangement, employment status, years in education, native language, marital status).Anthropometric measures (height, mass, shoe size and leg length).Health status (current medication and use of mobility aids (eg, walking frame)).Clinical measuresDisease duration.Late-life functional disability instrument.^49^Levodopa equivalent daily dose.^50 51^Frailty phenotype.^52^Parkinson’s disease-specific measuresMovement Disorder Society-Unified Parkinson’s Disease Rating Scale (30).Hoehn and Yahr Stages.^48^New Freezing of Gait Questionnaire.^53^Montreal Cognitive Assessment.^54^Physical measuresShort Physical Performance Battery.^55^Seven-day remote monitoring period (interact with digital health technology system).Diary, questionnaire and qualitative questionsMotor complications diary (ON-OFF-dyskinesia).Usability questionnaire.^38^Open-text questions.

Researchers who collect data pertaining to outcome measures will receive appropriate training before data collection (eg, Good Clinical Practice training, informed consent in clinical research training and Movement Disorder Society-Unified Parkinson’s Disease Rating Scale and Montreal Cognitive Assessment training). To promote participant recruitment and retention, participants will be given detailed oral and written instructions via a PIS. The PIS will include details for day-to-day use of the devices (ie, how to charge the devices and how to respond to medication notifications) and contact details for the research team should any issues or questions arise.

### Seven-day remote monitoring period

Primary outcome measures include self-reported medication adherence (ie, frequency, intake time and dosage of medication) captured by the smartwatch and walking speed, quantified via the IMU. Secondary outcome measures include macro outcomes (related to volume (eg, step count), pattern (eg, walking bout length) and variability (eg, walking bout length variability) of walking activity and micro outcomes (related to pace (eg, gait speed), rhythm (eg, step time), variability (eg, step time variability), asymmetry (eg, step time asymmetry) and postural control (eg, step length asymmetry)).^30–33^ DMOs obtained during the 7-day monitoring period. In addition, contextual factors captured on the smartphone, including geolocation (probability of being indoors/outdoors), number of steps outside the home, stay points, common paths and weather conditions (for more detail, see Smartphone section below).

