This study aims to collect real-world data using a novel DHTS (smartphone, smartwatch and inertial measurement unit, IMU) to assess self-reported medication adherence, quantify DMOs and model and predict their response to medication. Within this study, specific objectives include: (1) clinically characterise our participants with Parkinson’s (eg, Hoehn and Yahr stage, disease duration); (2) collect real-world data with a connected DHTS in PwP; (3) assess real-world, self-reported medication adherence in PwP by recording medication intakes (smartwatch reminders, time of logged intakes and acknowledged medication intake events); (4) quantify real-world DMOs (eg, walking speed) and (5) model and predict response of DMOs to Parkinson’s medication.

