#### Smartwatch to assess real-world, self-reported medication adherence

To assess real-world, self-reported medication adherence, participants will wear and interact with a smartwatch (TicWatch Pro V.3, Mobvoi) throughout the monitoring period. During the clinic visit, a researcher will manually input the participant’s medication reminders onto the Aeqora application. This application will then send notifications from the smartphone to the smartwatch to remind participants of their Parkinson’s-specific medication intake times and allow them to log the times at which their medication was taken, clicking either ‘yes’ or ‘no’ on the watch face when prompted (figure 2). The watch will also allow participants to log any additional Parkinson’s-specific medication they have taken (‘as required’). Participants will be provided with a smartwatch charger and will be required to remove and charge the smartwatch overnight throughout the monitoring period. Common, validated methods for monitoring medication adherence rely on questionnaires and diary completion. These place extra burden onto participants and are often subjective. For this reason, this study uses the objective method of responding to notifications on a smartwatch, as this provides objective, real-time insights into medication adherence and minimises participant burden.

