Only participants whose mobility data are collected for at least 3 days will be included in analysis. If participants do not complete one of the study assessments (eg, Short Physical Performance Battery) or their data from the devices is not collected, their remaining data will still be included in analysis. Assuming missing data is at random, modern statistical techniques will be used to handle missing data and will be compared with a complete case approach.^41^

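### Dosage is part of the primary adherence outcome but is not shown to be measured by the watch, and the stated missing-data check could not detect response-related bias in adherence

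*Protocol article*

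**What the plan says.** The section Seven-day remote monitoring period names two primary outcomes, one of which is "self-reported medication adherence (ie, frequency, intake time and dosage of medication) captured by the smartwatch".

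The smartwatch section describes how this is captured. At the clinic visit, "a researcher will manually input the participant’s medication reminders onto the Aeqora application". Participants then "log the times at which their medication was taken, clicking either ‘yes’ or ‘no’ on the watch face when prompted". For unscheduled doses, "The watch will also allow participants to log any additional Parkinson’s-specific medication they have taken". Objective 3 in the Introduction lists the recorded elements as "smartwatch reminders, time of logged intakes and acknowledged medication intake events", without dosage.

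The smartwatch section also says that participants "will be required to remove and charge the smartwatch overnight throughout the monitoring period". The motor complications diary covers 06:00 to 22:00 and records OFF status and dyskinesia, not intake.

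On missing data, the Data analysis section says: "Assuming missing data is at random, modern statistical techniques will be used to handle missing data". The one comparison named is with complete cases. The minimum of 3 days for inclusion applies to mobility data; none is stated for watch data.

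**The concern.** There are two linked problems.

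**Measurement.** Dosage is a named component of a primary outcome, yet no described function of the watch takes in an amount. Even if each reminder carries the prescribed dose, a yes confirms that dose and does not measure what was swallowed. A partial or altered dose would not show.

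**Missing responses.** A reply to a prompt about taking a dose may be absent because the dose was missed, because it was taken but not logged, or because the watch was on its charger. The first two reasons depend on the quantity being measured, so missing at random is hard to defend for this outcome. A complete-case analysis also ignores such dependence. Agreement between the two analyses would therefore be no reassurance.

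The consequences go beyond the adherence figure. The Data analysis section uses watch timestamps to study the effect of medication on the digital mobility outcomes (DMOs), and the Statistical analysis section models DMOs between intakes. A dose that was taken but not logged mis-times the interval that follows it.

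**Working it through.** The article states no adherence figure, so there is none to reproduce. It also gives no response rate, no expected adherence and no share of doses due overnight. All rates below are assumptions.

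**1. Dosage, place by place**

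| Place | Elements of adherence |
|---|---|
| Introduction, objective 3 | reminders, logged times, acknowledged intakes |
| Seven-day remote monitoring period | frequency, intake time, dosage |
| Smartwatch section | prompt, yes/no reply, logged time, log of extra doses |

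Frequency and intake time have a described source on the watch. Dosage has none.

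**2. What the replies alone can establish**

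Let u be the share of prompts unanswered and y the share of yes among those answered, taking the answers as truthful.

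- Lower bound (unanswered = not taken): (1 − u) × y
- Upper bound (unanswered = taken): (1 − u) × y + u
- Complete case: y. A missing-at-random analysis without informative covariates gives the same.

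With y = 0.95:

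| u | Lower | Upper | Complete case |
|---|---|---|---|
| 0.10 | 0.90 × 0.95 = 85.5% | 95.5% | 95% |
| 0.20 | 0.80 × 0.95 = 76.0% | 96.0% | 95% |
| 0.30 | 0.70 × 0.95 = 66.5% | 96.5% | 95% |

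**3. Direction of bias**

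Let A be true adherence, rt the chance that a prompt is answered if the dose was taken, and rm the chance if it was missed.

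- Complete case = A·rt / (A·rt + (1 − A)·rm)
- Lower bound = A·rt
- Upper bound = A·rt + share unanswered

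With A = 80%:

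| rt | rm | Complete case | Bias (points) | Bounds |
|---|---|---|---|---|
| 0.9 | 0.5 | 0.72/0.82 = 87.8% | +7.8 | 72% to 90% |
| 0.9 | 0.3 | 0.72/0.78 = 92.3% | +12.3 | 72% to 94% |
| 0.7 | 0.7 | 0.56/0.70 = 80.0% | 0 | 56% to 86% |
| 0.5 | 0.7 | 0.40/0.54 = 74.1% | −5.9 | 40% to 86% |

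The bias is upward only if rm < rt. It is zero if they are equal and downward if rm > rt. The bounds contain the true 80% in every row, without any assumption about direction.

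**4. Doses due while the watch is off**

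Assume 5 doses a day, 1 of them while the watch is off, and 90% adherence for the other 4.

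| Adherence to the watch-off dose | True overall | Watch-on doses only | Watch-off dose counted as missed |
|---|---|---|---|
| 90% | (3.6 + 0.9)/5 = 90% | 90% | 3.6/5 = 72% |
| 70% | (3.6 + 0.7)/5 = 86% | 90% | 72% |
| 50% | (3.6 + 0.5)/5 = 82% | 90% | 72% |

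Leaving these doses out can overstate adherence, and counting them all as missed understates it whenever any were taken.

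**The case against.** The other side has several good points.

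- **Overstatement is not shown.** A reader might infer that the plan will overstate adherence. Step 3 shows that this needs missed doses to be answered less often than taken ones, which the documents do not establish. If doses are taken during OFF periods when tapping is hard, the bias runs downward. This objection stands.
- **Unanswered prompts are not lost.** A reader might infer that the watch does not record them. Objective 3 lists both reminders and acknowledged intakes, so a reminder without an acknowledgement can be identified. Only its classification is unstated, and a full protocol or SAP may supply that. This also stands.
- **Imputing single prompts is not stated.** The missing-at-random sentence follows remarks about assessments not completed and device data not collected. Reading it as a rule for individual prompts is an inference. However, it is the only missing-data rule given, and it makes no exception for adherence.
- **Dosage may be linked to the reminder.** A researcher enters the reminders, current medication is recorded, doses must be stable, and the figure of the watch is not shown. A yes may therefore stand for a known prescribed dose. If so, the outcome should say that; the amount taken would still not be measured.
- **The overnight gap is of unknown size.** No hours are given for charging, and later logging is not excluded. It is not described either.
- **Remedies can bias too.** Removing watch-off doses from the denominator, or dropping intervals after unanswered prompts, excludes data that may be informative. The fix below avoids both.

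**Conclusion.** The point holds in a limited form. The article claims dosage as part of a smartwatch-captured primary outcome, while the places that describe the capture do not show the amount taken being measured. Those places need to be reconciled. Separately, the only stated missing-data rule rests on an assumption that is doubtful for self-logged intake, and its only comparison cannot test that assumption.

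The size is unknown. Under the assumed rates in step 3, the complete-case error runs from 5.9 points too low to 12.3 points too high. The range of 76% to 96% at 20% non-response likewise rests on assumed inputs. It describes what the data leave open and is not evidence that adherence is overstated. In step 2 every upper bound lies above the complete-case 95%.

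This should be changed, but it does not invalidate the study.

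**What to change.** 1. Define dosage as the prescribed dose confirmed as taken, or remove it from the smartwatch outcome. Bring objective 3, the primary outcome and the smartwatch section into line.
2. Class each scheduled dose as yes, no, unanswered or watch off. Beside the planned analysis, report adherence with all unanswered doses counted as not taken and again as taken.
3. Show watch-off doses separately, alongside the all-dose figure and not removed from it.
4. In the DMO models, flag intervals that follow an unanswered prompt and fit the models with and without them as a sensitivity analysis. Do not drop them by default.

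The Statistical analysis section allows methods to be amended once data collection is complete, so the classification and bounds should be fixed before then. According to Study status, data from 30 participants are in hand, so the unanswered and watch-off shares can be counted now to replace the assumed rates.

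The cost is some wording, a few more table rows and one extra model run. Adherence would be shown with a range, which may be wide if many prompts go unanswered.

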### Measurement tools and data collection

To collect data on self-reported medication adherence, DMOs and contextual insights, participants will interact with the novel DHTS (smartphone, smartwatch and IMU) over seven consecutive days. This monitoring period will commence following a Mobilise-D appointment or following the initial assessment for those recruited independently.

#### Smartphone to collect contextual data

As this study will be carried out remotely, in the participant’s home and their community, contextual factors such as weather conditions and being indoors or outdoors, may influence DMOs. Therefore, capturing these contextual factors will help better describe, understand and control for these aspects when looking at the effect of medication on DMOs. To quantify the effect of these confounding contextual factors on DMOs, participants will be advised to carry a smartphone (Samsung Galaxy S9, S10 or S21) whenever outside their house, making sure it is switched on at all times and fully charged. Participants will be provided with a charger and will be advised to charge the smartphone every night throughout the monitoring period.

The custom-made Aeqora application extension will be preinstalled onto each smartphone (Department of Computer Science, The University of Sheffield, UK). This application will use the phone’s sensors to capture contextual information, such as, geolocation, stay points, common paths, number of steps and weather conditions. The application has been developed as an Android mobile application. It is made up of three components: (1) the core tracker, (2) the interface and (3) the server infrastructure, which collects data across users.^34^ The core tracker has been adapted from a library developed by the University of Sheffield.^35^ This tracker identifies the type of activity (eg, walking) from the phone’s internal sensors (accelerometer and gyroscope). It continually operates in the background to sense mobility features using these sensors and location services, such as Bluetooth.^34^ To identify the weather conditions at the time of measurement, the closest weather station to the participant’s location will be used. Raw sensor data will be collected and stored in real-time onto a local database which is synchronised with a remote database when the phone is recharging. No participant identifiable information will be sent to the server. The data are synched to the remote database via a Secure Socket Layer (SSL) and Transports Layer Security V.3.0 protocol. To ensure privacy and security when communicating sensitive data an SSL/TSL certificate is exchanged between client and server, which establishes the identity and trust between them.

#### Smartwatch to assess real-world, self-reported medication adherence

To assess real-world, self-reported medication adherence, participants will wear and interact with a smartwatch (TicWatch Pro V.3, Mobvoi) throughout the monitoring period. During the clinic visit, a researcher will manually input the participant’s medication reminders onto the Aeqora application. This application will then send notifications from the smartphone to the smartwatch to remind participants of their Parkinson’s-specific medication intake times and allow them to log the times at which their medication was taken, clicking either ‘yes’ or ‘no’ on the watch face when prompted (figure 2). The watch will also allow participants to log any additional Parkinson’s-specific medication they have taken (‘as required’). Participants will be provided with a smartwatch charger and will be required to remove and charge the smartwatch overnight throughout the monitoring period. Common, validated methods for monitoring medication adherence rely on questionnaires and diary completion. These place extra burden onto participants and are often subjective. For this reason, this study uses the objective method of responding to notifications on a smartwatch, as this provides objective, real-time insights into medication adherence and minimises participant burden.

**Figure 2 F2:**
[figure not shown]
Digital Health Technology System. (A) Inertial measurement unit, which monitors mobility. (B) Smartwatch which assesses self-reported medication adherence, by notifying participants when to take their medication and allowing them to log the time at which they took their medication. (C) Smartphone which collects contextual data.

#### IMU to quantify DMOs

To quantify primary and secondary DMOs, participants will continuously wear an IMU (Axivity AX6, Axivity, Newcastle upon Tyne, UK, including triaxial accelerometer and gyroscope, dimensions 23×32.5×8.9 mm, mass 11 g, frequency 100 Hz, gyroscope range±2000°/s and accelerometer range ±8 g) throughout the monitoring period. The IMU will be secured to the participant’s lower back, at the fifth lumbar vertebrae.^34^ It will be affixed using a hydrogel/hydrocolloid adhesive and a hypoallergenic plaster patch. Participants will be advised to continue with their usual activities and not change their routine. Throughout the monitoring period, all IMU data will be stored locally on the IMU hardware. After the monitoring period, participants will return the IMUs via prepaid envelopes and data will be downloaded and uploaded onto the eScience (e-SC) (a cloud-based storage platform) CiC Data Management platform^36 37^ (see data management section). The IMU will be worn at all times, including during the night and although the IMU is waterproof participants will be advised to remove it during prolonged water exposure (eg, swimming, taking a bath).

### Diary to monitor motor complications

During the 7-day monitoring period, participants will fill in a motor complications diary (paper based) for each day, indicating their ‘OFF-status’ (when they feel their medication is not working) and whether they experienced dyskinesia (involuntary movements). The diary will record data over 16 hours each day from 6:00 to 22:00 hours, from days 1 to 7 (online supplemental material 4).

10.1136/bmjopen-2023-073388.supp4Supplementary data

### Assessment of participants’ experience with the DHTS

#### Questionnaire to evaluate usability of the DHTS

To evaluate the participants’ experience with the DHTS, participants will complete an adapted version of Rabinovich *et al*’s 12-item usability questionnaire at the end of the monitoring period (online supplemental material 5).^38^ This questionnaire investigates usability on a 5-point ordinal scale, from 5 (most favourable) to 1 (least favourable), and ‘no opinion’ scored as 3. The questions identify participant’s attitude towards the DHTS, its ease of use and comfort, such as, ‘I experienced technical problems’ and ‘The monitors interfered with my normal activity’. Participants will also rate the DHTS on a scale from 0 (worst score) to 100 (best score).

10.1136/bmjopen-2023-073388.supp5Supplementary data

Qualitative feedback on the DHTS and its individual devices will be collected via open-text questions added to the end of the questionnaire (online supplemental material 5). These questions require participants to ‘give any other comments on the DHTS and its components’, to describe the ‘problems’ they experienced when using the DHTS and its components, as well as any features they liked about the system and its individual devices. All devices will be returned at the end of the assessment period, in addition to the questionnaire and motor complications diary, using prepaid tracked envelopes.

